### Sample size and power calculation

Previous studies have shown that low to moderate intensity treatment for depression yields effect sizes on a variety of questionnaire-based outcomes of about 0.33 standard deviations, and about 50 % relative advantage in recovery rate compared to usual care [28]. Experience from our previous PHC studies as well as from the control arm of the Chilean trial suggest a recovery rate of about 30 % for major depression with no active treatment and about 70 % with treatment [29]. For our sample size estimation, we sought to detect an absolute difference of 18 percentage points (41 % recovery in control and 59 % in intervention groups respectively) at 12 months, a difference that we think is both plausible for this type of intervention and would promote changes in practice. We assumed an intra-cluster correlation coefficient (ICC) of 0.05 based on pilot study data, and collection of the primary outcome for 80 % of participants. The uninflated sample size requires 131 per arm for analysis to detect a difference of 59 % vs 41 % (equivalent odds ratio = 2.1) with 80 % power at the two-sided 5 % alpha level. We aimed to recruit 90 individuals per clinic. With 72 per cluster available for the primary analysis and an ICC of 0.05, the design effect is 4.55, giving a total number required for analysis of 1190. We therefore aimed to recruit 90 individuals from each of 16 clinics initially. As participant recruitment was slower than anticipated, in March and November, 2014 we recruited and randomised a further 19 clinics, giving a total of 35 in the study. Participant recruitment started December 2013 and is still ongoing.

### Data analysis

Individual data is collected and stored electronically using palmtops programmed to capture information directly from respondents. This is to ensure accuracy and security of data collection. All data are kept anonymously using codes to identify individuals. Data is downloaded from palmtops to desktops located in the central office in Ibadan where it will be cleaned and stored. These datasets do not contain the allocation status of the participants which is kept as a separate file and only for the trial statistician. Access to the datasets is possible for members of the research team through a password-protected entry.

A full statistical analysis plan will be developed before any data are analyzed. The analysis and presentation of the trial will be in accordance with CONSORT guidelines for cluster randomized trials [30, 31]. The primary approach for comparative analyses will be to analyze participants as randomized without imputation of missing data, and with due emphasis placed on confidence intervals for the between-arm comparisons. We will use descriptive statistics to assess balance between the trial arms at baseline for both clinic and individual participant characteristics. In order to take appropriate account of the hierarchical nature of the data, we will use multivariable mixed effects regression models to estimate recovery from depression at 12 months for intervention group versus control, adjusting for baseline depression and LGA as a stratification variable. In a secondary analysis, we will further adjust for any variables that were imbalanced between trial arms at baseline. These analyses will be repeated for secondary outcomes. We will conduct sensitivity analyses to assess the potential effect of missing data, and will investigate the effect of adherence with the intervention. We will investigate whether between-group differences vary over time using data from all follow-up visits in repeated measures analyses.

We will investigate whether there is any differential effect of the intervention according to baseline symptom severity (PHQ-9 score <16, ≥16) and duration (≤3 months, >3 months) by including appropriate interaction terms in the primary regression model. Since the trial is powered to detect overall differences between groups rather than interactions of this kind, the results will be interpreted with due caution.

Data analysis will be conducted once all follow-up is complete. There are no planned interim analyses.

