**Methods/Design:**

STEPCARE is a two-arm parallel cluster randomized controlled trial to compare a stepped-care intervention package for depression in primary health care with care as usual in Nigeria. Randomization was conducted at the level of the participating primary health care clinics, while interventions are delivered to consenting individual participants who screen positive on the 9-item patient health questionnaire (PHQ-9 score ≥ 11) and fulfil the DSM-IV criteria for major depression. Intervention delivered by trained primary health care workers (PHCW) supported by general physicians and psychiatrists as needed is in 3 steps determined by response to treatment. Each step consists of psychological interventions (including psychoeducation, activity scheduling, social network reactivation and problem solving treatment) offered to all participants and, depending on severity and response, medication. Primary outcome, assessed at 12 months following recruitment into the trial, is recovery from depression as shown by a PHQ-9 score of less than 6. Secondary outcomes include changes in disability, quality of life and service utilization assessed at 6 and 12 months.

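### The further-adjusted secondary analysis picks covariates by observed baseline imbalance, and the disability and quality-of-life models do not name their own baseline score (minor; the primary model is unaffected)

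*Protocol article*

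**What the plan says.** All of this is in the Protocol article, mainly under Data analysis.

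- Primary model: mixed effects regression for recovery at 12 months, "adjusting for baseline depression and LGA as a stratification variable". These covariates are fixed in advance.
- Balance check: "We will use descriptive statistics to assess balance between the trial arms at baseline for both clinic and individual participant characteristics". No variable list and no cut-off is given.
- Further adjustment, in an analysis labelled secondary: "we will further adjust for any variables that were imbalanced between trial arms at baseline".
- Secondary outcomes: "These analyses will be repeated for secondary outcomes". No covariate specific to an outcome is named.
- The Abstract describes these outcomes as changes: "Secondary outcomes include changes in disability, quality of life and service utilization assessed at 6 and 12 months". Under Outcome measures, Secondary, only depression symptoms are described as a change; disability is described as a level.
- Further detail is deferred: "A full statistical analysis plan will be developed before any data are analyzed".

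**The concern.** There are two separate weaknesses.

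**Selection by imbalance.** The rule ties entry into the model to how a variable happens to differ between arms, not to whether it predicts outcome. An irrelevant variable that differs by chance goes in, and a strong predictor that is balanced stays out. Symptom duration shows this: the article thinks it important enough for an interaction analysis, yet it enters the further-adjusted model only if it turns out imbalanced. With no list and no threshold, the covariate set is a judgement made after viewing data by arm, and the resulting estimate can be read as selective. Writing the SAP before analysis does not cure this. An SAP that repeats the rule fixes a procedure whose result still depends on those data.

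**Own baseline not named.** If the primary model is carried over as written, the disability and quality-of-life models contain baseline PHQ-9 and LGA. Their own baseline score, usually the best single predictor of a follow-up score, would enter only if it happened to be imbalanced. The stake is precision on the secondary outcomes.

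**Working it through.** **1. The plan's own figures.** From Sample size and power calculation: 41% v 59%, "with 80 % power at the two-sided 5 % alpha level", 72 analysed per clinic, ICC 0.05.
- The usual two-proportion formula gives 120 per arm, and 131 with continuity correction, which matches the stated 131.
- Design effect = 1 + (72 − 1) × 0.05 = 4.55, as stated.
- Total = 2 × 131 × 4.55 = 1192, against 1190 stated. It reproduces, and nothing below changes it.

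**2. How often a truly balanced variable looks imbalanced.**
- Inputs: 1190 participants over the 35 randomized clinics (Setting) gives 1190/35 = 34 per clinic.
- Assumptions: covariate ICC 0.01 to 0.05 (the article's 0.05 is for the primary outcome); a cut-off, because the plan gives none; stratification by LGA ignored, which would lower the rates for variables that differ between LGAs.
- Design effect D = 1 + 33 × ICC, so 1.33 at ICC 0.01 and 2.65 at ICC 0.05.
- Naive 5% check that ignores clustering: P(|Z| > 1.96/√D).
- Absolute standardized difference above 0.1: P(|Z| > 0.1/SE), with SE = √(4D/1190).

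| Covariate ICC | D | Naive 5% check | Standardized difference > 0.1 |
|---|---|---|---|
| 0 | 1.00 | 5% | 8.5% |
| 0.01 | 1.33 | 9% | 14% |
| 0.05 | 2.65 | 23% | 29% |

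With 10 independent candidate variables (also an assumption), about 1 to 3 would be added by chance under either cut-off (10 × 0.09 = 0.9 up to 10 × 0.29 = 2.9).

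**3. What leaving out the own baseline could cost.** The article gives no correlation between baseline and follow-up scores, so this is a range for a continuous outcome.
- Inputs: the 16 clinics first planned × 72 = 1152, and 1152/35 = 33 per clinic. ICC 0.05 is assumed for these outcomes too.
- Design effect = 1 + 32 × 0.05 = 2.6. The individual-level part of the variance of the comparison is 0.95/2.6 = 37%.
- A covariate with correlation r removes r² of that part: 16% at r = 0.4 and 36% at r = 0.6. Between-clinic variance is taken as unchanged.
- Share of the whole variance removed: 0.16 × 0.365 = 6% and 0.36 × 0.365 = 13%. As information, 1/(1 − 0.058) = 1.06 and 1/(1 − 0.132) = 1.15, so 6 to 15% more.

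**4. Allowing for baseline PHQ-9 already in the model.** Let a be the correlation of PHQ-9 with the outcome (assumed 0.1 to 0.3), b that of the own baseline with the outcome, and c that between the two baselines (assumed 0.3 to 0.5). Then R² = (a² + b² − 2abc)/(1 − c²), and the residual variance ratio is (1 − R²)/(1 − a²). Multiplying the individual-level reduction by 0.365, to a close approximation:

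| b | Variance ratio | Share of whole variance removed |
|---|---|---|
| 0.2 | 0.996 to 0.968 | 0.1 to 1.2% |
| 0.4 | 0.908 to 0.835 | 3 to 6% |
| 0.6 | 0.703 to 0.593 | 11 to 15% |

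The range therefore runs from negligible to moderate, with or without this allowance.

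**The case against.** The other side has several good points.

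- **The primary result.** A reader might infer that the trial's main estimate is data-driven. The article does not support that. The imbalance rule is confined to a secondary analysis, and the primary covariates are named in advance.
- **The chance rates.** A reader might take 9 to 23% as the behaviour of the planned procedure. It is not: the plan uses descriptive statistics and states no test. The rates show only that clustering makes chance imbalance common.
- **Imbalance may be real.** Clinics were randomized and staff trained before participants were screened and consented, so a difference between arms can reflect differential recruitment. Looking at adjustment for it then has a legitimate sensitivity role. This stands, but it supports a labelled check, not choosing the main adjusted model by inspection.
- **Secondary outcomes.** A reader might infer that PHQ-9 is their only covariate. LGA carries over too, and an own baseline could enter if imbalanced. For depression symptoms at 6 months, PHQ-9 already is the own baseline. Repeating the analyses may also mean an analogous model with each outcome's own baseline, and the SAP may say so. This leaves an ambiguity, not a proven omission.
- **Baseline collection.** That disability and quality of life are measured at baseline is only implied by the Abstract's reference to changes. For service use the article does not state it. If a change score is analysed, the baseline enters through the outcome, but this does not replace adjustment. With equal variances, the individual-level variance is 2(1 − r) = 1.2 at r = 0.4 and 0.8 at r = 0.6, against 1 − r² = 0.84 and 0.64 with adjustment.
- **Precision.** Quoting r² alone (16 to 36%) would overstate the loss, since it applies only to the individual-level part. Nor does it carry over directly to the binary recovery outcome, for which no loss is claimed.

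**Conclusion.** The point holds as a minor one. The article itself states an imbalance-triggered rule for its further-adjusted secondary analysis, so the matter is fixed badly and not merely left to the SAP. The primary model and the sample size are not affected.

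On size, chance alone would flag roughly 9 to 23% of balanced variables under a naive 5% check at 34 per clinic. That rests on an assumed covariate ICC of 0.01 to 0.05 and on a cut-off the plan does not contain.

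The own-baseline part depends on a literal reading and on baseline scores having been collected. If both hold, the cost for disability and quality of life is unknown: negligible for weak correlations, and about 6 to 13% of the variance of the comparison for correlations of 0.4 to 0.6 (33 per clinic, ICC 0.05, between-clinic variance unchanged, before allowing for PHQ-9 in the model).

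**What to change.** 1. Replace the imbalance rule with a short list of prognostic covariates, for example age, sex and symptom duration. Fix it before any data are seen by arm, and use it whatever the baseline table shows.
2. Keep the baseline table descriptive. If adjustment for observed imbalance is still wanted, label it a post hoc sensitivity check for differential recruitment.
3. State that each continuous secondary outcome is adjusted for its own baseline value where measured, plus LGA, and for baseline PHQ-9 if wanted. Say which scales are collected at baseline.

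The cost is wording in the protocol or SAP and a little analysis work. No new data and no change in sample size are needed. The article reports recruitment still under way and no analysis until follow-up is complete, so by its own account there was time to make the change.

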
## Discussion

This randomized-controlled trial evaluates the effectiveness of a stepped care intervention model for depression in primary care compared to enhanced care as usual. The key strength of this study is the use of a task-sharing model that relies almost entirely on the capability of non-physicians PHCWs to deliver an evidence-based intervention, in keeping with the scarcity of specialist mental health manpower in the country. The stepped care model examines the effectiveness of an intervention package for depression in which the intensity of treatment is determined by the clinical need of the patients.
